### Randomization and blinding

#### Randomization

Randomization of a patient is stratified according to UICC stage (8th edition) into stratum I (UICC I and II) and stratum II (UICC III and IV). This considers that patients treated by surgery alone are generally assigned to the earlier tumor stages UICC I and II and are less likely to require adjuvant therapy. Patients with an indication for adjuvant radiotherapy or radiochemotherapy or primary radiotherapy or simultaneous radiochemotherapy are more likely to belong to the advanced tumor stages UICC III and IV. Randomization will be computerized (REDCap database) by a physician from the Section of Phoniatrics and Pediatric Audiology prior to intervention, after informed and signed consent (see above).

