## Background

Head and neck squamous cell carcinoma (HNSCC) is the sixth most common malignant tumor disease, mostly affecting the upper aerodigestive tract [1]. At a typical Head and Neck Cancer Center, approximately 55% of patients currently suffer from dysphagia [2]. In subgroups with, e.g., oropharyngeal carcinomas, such disorders occur in up to 80% of cases, fatal because in this group the proportion of younger patients is increasing worldwide due to the association with HPV (human papillomavirus) and already reaches 30–40% in Germany [3]. Especially these younger patients rightly expect special attention to swallowing disorders because of disease and therapy. Last, but not least, clinically relevant anxiety or depression symptoms are regularly associated with dysphagia, in almost 50% of cases [4], hardly surprising considering the central social importance of eating and drinking together. Elderly patients (over 65 years of age) are at mortality risk from dysphagia, especially from aspiration pneumonia [5]. Often, patients with HNSCC have low socioeconomic status and relevant comorbidities that lead to retirement in up to 50% of cases after therapy [6]. In contrast, early rehabilitation of dysphagia appears to mitigate the financial consequences of the disease [7]. Swallowing disorders in head and neck tumor patients are thus highly relevant for effective therapeutic interventions not only because of the directly associated limitations of quality-of-life (QoL), but also because of the risk of complications.

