To obtain sufficient accuracy for the estimation of treatment effects due to the performed intervention as well as for the planning of a confirmative follow-study, *n* = 30 patients per study arm (*n* = 60 in total) are to be analyzed under the assumption of median effect sizes regarding the endpoints of the primary endpoint family [22]. Assuming a drop-out rate of 15%, *n* = 70 patients have to be included and randomized in the study. In the recruitment period of 17 months, we assume a potential study population of 350 patients (250 primary cases in the Head and Neck Cancer Center per year). Considering the increase in higher tumor stages due to the corona pandemic, we expect 40% of patients (*n* = 140) to meet all inclusion and exclusion criteria, of which 50% of patients (*n* = 70) are likely to give informed consent. Thus, inclusion of 70 patients in the planned recruitment period is realistic. Screening and identification of potential study patients will occur during the patient’s first inpatient stay (primary diagnosis, histology acquisition, pan-endoscopy, staging). After the tumor diagnosis has been confirmed, the first contact with the potential study patient is made in the Ear, Nose and Throat Clinic and the Clinic for Oral and Maxillofacial Surgery (usually after the interdisciplinary tumor board) by physicians from the clinics with the support of the study assistance. The detailed study information as well as the study inclusion is carried out by the medical staff of the Section of Phoniatrics and Pediatric Audiology. 

The study is explained in detail to the patient by a physician from the Section of Phoniatrics and Pediatric Audiology. Subsequently, the patient gives an informed consent to participate in the study by means of a written declaration of consent. As part of the consent process, the participant will be asked whether the data collected may also be used for questions unrelated to the study but related to the study purpose. The participant can agree to such use or refrain from doing so. Randomization is performed prior to the intervention, after informed and signed consent, via REDCap database. Each randomization is documented and signed by the investigator.

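### Stage strata stand in only loosely for planned treatment, and the primary ANCOVA adjusts for neither, so a chance imbalance in treatment is neither prevented nor corrected

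*Protocol article*

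**What the plan says.** In the Protocol article, the Randomization section defines two strata, UICC I/II and UICC III/IV, and justifies them by treatment. On the early stages it says "This considers that patients treated by surgery alone are generally assigned to the earlier tumor stages UICC I and II". On the advanced stages it says "Patients with an indication for adjuvant radiotherapy or radiochemotherapy or primary radiotherapy or simultaneous radiochemotherapy are more likely to belong to the advanced tumor stages". Adjuvant treatment after surgery and primary radio(chemo)therapy are thus expected in the same stratum.

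Under Sample size and recruitment, the first contact with a patient takes place "usually after the interdisciplinary tumor board". Randomisation comes later, after written consent and before the intervention.

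The Statistical analysis section specifies an ANCOVA for each primary endpoint at 6 weeks, with study group as factor and that endpoint's baseline value as covariate. It names no other term. Table 1 places the baseline measurements before oncological therapy. The Discussion (Innovation content of the study) expects both a high proportion of primary surgery and patients with primary radiation. The Data management section says REDCap keeps groups and strata balanced, but the strata are defined by stage alone.

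**The concern.** The protocol treats the expected treatment as important enough to justify the stratification, yet treatment enters the design only through stage. Within UICC III/IV, nothing holds the split between primary surgery and primary radio(chemo)therapy equal across arms.

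The stated analysis does not make up for this. The baseline score describes swallowing or distress before treatment, so it cannot capture what surgery or radiation does by the 6-week visit. The stratification factor itself is also absent from the model.

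Two aims of the trial are affected. The study is meant to supply reliable effect estimates for planning a multicentre trial. It also calls the concept promising if the advantage is consistent across the endpoint family. PAS, YRS, DHI and FOIS-G all measure swallowing in the same patients. One treatment imbalance could tilt several of them in the same direction and look like consistency.

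**Working it through.** **Inputs from the document.** 30 analysed per arm, 60 in total; 70 randomised; 1:1 allocation; assumed effect d ≈ 0.5; ANCOVA terms are study group and baseline value.

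**Inputs assumed, because the document gives none.** 40–50 of 70 patients in UICC III/IV; 30–50% of these on primary radio(chemo)therapy; equal arms within the stratum; modality effect on the 6-week endpoint, after baseline adjustment, of 0.8 SD, with 0.3 SD as a lower value.

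**Step 1: the plan's own figure.** 60/(1 − 0.15) = 70.6, against the stated 70, which agrees apart from rounding. The document gives no figure for treatment balance.

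**Step 2: chance of imbalance.** Let n patients be in the stratum, K of them on primary radio(chemo)therapy, and n/2 per arm. The number X on that treatment in one arm is hypergeometric (n, K, n/2). The between-arm difference in share is |2X − K|/(n/2). The probability that it reaches 20 percentage points is:

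| n in UICC III/IV | share 30% | share 40% | share 50% |
|---|---|---|---|
| 40 | 30% | 33% | 34% |
| 46 | 11% | 13% | 24% |
| 50 | 22% | 15% | 26% |

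The range is 11–34%. It is uneven because the difference can only take whole-patient steps. With n = 40, four patients already make 20 points; with larger n it takes five or six. The difference has mean 0 and an SD of 13–16 points.

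For the 60 analysed patients and wider assumptions (50–80% of patients in the stratum, 20–50% of these on primary radiotherapy), the chance is 5–47%.

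**Step 3: shift in the group difference.**

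- Within the stratum: 0.20 × 0.8 = 0.16 SD.
- Overall, weighted by the stratum's share: 0.16 × 40/70 = 0.09 SD to 0.16 × 50/70 = 0.11 SD.
- Relative to d = 0.5: 0.09/0.5 = 18% to 0.11/0.5 = 23%.
- With a 0.3 SD effect: 0.20 × 0.3 × 40/70 = 0.03 SD to 0.20 × 0.3 × 50/70 = 0.04 SD, or 7–9% of d.

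**Step 4: comparison with random error.** The 95% CI half-width at 30 per arm is 1.96 × √(2/30) = 0.51 SD.

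**Step 5: precision lost by leaving modality out.** The share of outcome variance due to modality within the stratum is (stratum share) × p(1 − p) × effect².

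- At 0.8 SD: 40/70 × 0.21 × 0.64 = 0.08 to 50/70 × 0.25 × 0.64 = 0.11. Removing it multiplies the half-width by √(1 − 0.08) = 0.96 to √(1 − 0.11) = 0.94.
- At 0.3 SD: 40/70 × 0.21 × 0.09 = 0.01 to 50/70 × 0.25 × 0.09 = 0.02, so the gain is negligible.

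**The case against.** The strongest defence is that the Randomization section has a different contrast in view: surgery alone against any radiotherapy. Grouping adjuvant with primary radio(chemo)therapy is then the intended design. Nothing in the document says the need for adjuvant therapy is settled when the patient is randomised, so stage is a reasonable factor for that contrast. Replacing stage by primary surgery versus primary radiotherapy would merge surgery alone with surgery plus adjuvant treatment. First contact is also only usually after the tumour board, so a plan will not exist for everyone. All of this stands. Two strata are defensible for 70 patients in an exploratory trial, and the stratification should be left as it is.

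It can also be said that further covariates are normally fixed in the statistical analysis plan, which is not shown. That limits the point but does not remove it: the article states the primary model term by term, and the proposal amends that stated model.

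A reader might infer several stronger things that the document does not support:

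- **The arms are unbalanced on treatment, or the comparison is biased.** Randomisation balances treatment in expectation and stage helps in part. Only enforced balance is missing, and the confidence intervals already allow for chance.
- **The protocol claims that stage secures balance on treatment.** It does not. Its wording is probabilistic, as in "are more likely to belong to the advanced tumor stages UICC III and IV", so there is no false statement to correct.
- **Most patients will be UICC III/IV.** The remark "Considering the increase in higher tumor stages due to the corona pandemic" only supports the 40% eligibility estimate; no stage distribution is given.
- **Irradiated HPV-associated tumours fall into the early stratum.** The Background figure belongs to a sentence on oropharyngeal carcinoma and says nothing about staging.
- **The shift is about a third of d.** 0.16 SD is 32% of 0.5, but it applies within one stratum, while d refers to the whole comparison.

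**Conclusion.** The point holds as a weakness in the stated primary model, not as a contradiction or a wrong figure. The protocol names expected treatment as the reason for its strata, and the planned primary treatment should usually be known at randomisation. Yet the ANCOVA includes neither the stratum nor the plan, and the pre-treatment baseline score cannot replace them.

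In size the problem is moderate at most. Under the stated assumptions, an imbalance of at least 20 points in the advanced stratum has a chance of about 11–34%, and a 20-point imbalance costs about 0.09–0.11 SD overall. That is roughly a fifth of the assumed effect and well inside the 0.51 SD half-width. Stratum size, treatment share and modality effect are all assumed. If modality matters little at 6 weeks, both the shift and the gain from adjustment are small. Adjustment is still worthwhile because it is cheap and the estimates are to inform the next trial.

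**What to change.** Before the data are analysed, extend each primary ANCOVA in the Statistical analysis section by two fixed covariates: the UICC stratum used at randomisation, and the planned primary treatment set by the tumour board before randomisation (primary surgery versus primary radio(chemo)therapy). Use the plan and not the treatment received, because the latter is determined after allocation. Where no board plan existed at randomisation, code the patient as not yet decided.

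The stratum costs one degree of freedom and the planned treatment one, or two if the third category is needed. The stated model leaves 60 − 3 = 57, so this is affordable. One baseline item must be extracted from the tumour-board record; the article does not say whether the eCRF already holds it.

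Leave the stage stratification unchanged in this trial. Recruitment was due to end about 31.03.2024 and the article appeared on 22.03.2024, so changing the REDCap strata would achieve almost nothing. Crossing stage with planned modality is a consideration for the confirmatory trial only.

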#### Blinding

The study is designed outcome-blinded, meaning that each detailed phoniatric swallowing examination (FEES) is subsequently assessed again objectively by another physician from the Section of Phoniatrics and Pediatric Audiology based on the video documentation using the specified documentation parameters (PAS, YRS). The second assessor does not know whether the examined patient is from the control or intervention group. Unblinding is not provided.

### Trial flow

In the intervention group, the inclusion examination is followed by nutritional counseling and a first control interview by a speech therapist based on the exercise diary taking place in the presence or on the phone after approximately 3–7 days. Further appointments are scheduled at 6 weeks, 3 and 6 months, and 9 or 12 months after the end of oncological therapy (Fig. 1).

**Fig. 1 Fig1:**
[figure not shown]
PREHAPS—trial flow chart

There will be no special post-trial care, but the standard surveillance program.

### Data management

In this study, the Research Electronic Data Capture (REDCap) system is used to implement electronic case report forms (eCRFs). All participant data throughout the study will be collected and directly entered into eCRFs. Data entries will be time-stamped and user-tracked, providing a detailed audit trail for monitoring data changes.

The randomization module of REDCap will be used to assign participants to one of both study groups (intervention/control group). The system’s ability to implement complex randomization algorithms facilitated the stratification process, ensuring a balanced allocation of participants across different study groups and strata.

### Quality assurance

#### Monitoring

Onsite monitoring follows a risk-based approach and is laid down in a monitoring plan. 100% SDV include informed consent and randomization. Within the established data management process, specific data quality rules are applied to collected data. Any deviation, unexpected missing, or implausibility of data will be reported to the study site for clarification.

#### Data monitoring committee

The data monitoring committee (DMC) is a panel of experts (phoniatrics, ENT, maxillofacial surgery, speech therapy, study assistance, biometry) and will evaluate which changes in primary outcome parameters should be interpreted as clinically relevant (see above). Interim analyses are not provided.

## Discussion

### Innovation content of the study

To the best of our knowledge, the described study is the first in Germany to address a pre-therapeutic swallowing intervention for patients with head and neck cancer. The feasibility (practicability, patient acceptance, etc.) and the integration of this complex and interdisciplinary intervention into the pre-therapeutic care process are investigated. The patient population is typical for a German Head and Neck Cancer Center including a high proportion of patients treated with primary surgery in addition to patients receiving primary radiation. Guideline recommendations concerning early phoniatric intervention in HNSCC patients are integrated insufficiently into the care process so far [8, 9, 23].

### Relevance of the study

The main pillars of primary therapy for HNSCC are, on the one hand, primary surgical procedures with functional reconstruction if necessary, often followed by adjuvant radiotherapy, and, on the other hand, primary radio-(chemo)therapy. Due to the critical localization of tumors in the upper aerodigestive tract, they lead to hoarseness as a relatively early symptom and/or often impair swallowing function. Swallowing dysfunction not only significantly reduces the QoL of patients, but also leads to life-threatening complications such as aspiration pneumonia in up to 25% of cases [24]. An analysis of the SEER cancer registry combined with US health insurance data showed a 3- to fourfold higher incidence of aspiration pneumonia for patients with HNSCC treated by primary radiochemotherapy compared with a control group of the same comorbidity. The hospitalization rate was 84%, and intensive therapy was required in nearly half of the cases. The relative risk of death increased up to 42% and there was a 15% reduction in 5-year survival [10].

A recent study of our group showed that existing postoperative dysphagia with an inability to take in oral food is a very early indicator of poor survival, irrespective of the tumor stage [23]. In addition, prolonged dysphagia regularly leads to malnutrition, sometimes with significant weight loss [25]. The prognostic significance of malnutrition lies in the prediction of early mortality and early recurrence, as well as a cellular immune deficiency, which limits curative therapy options even in times of immuno-oncological therapies [26]. For the differentiated examination of patients who are malnourished despite an inconspicuous BMI, measurement tools such as nutritional risk screening have already been introduced into standard oncological care or can be supplemented by modern methods such as bioelectrical impedance analysis [27].

A Canadian metanalysis provides initial evidence for the benefit of preventive treatment of dysphagia in primary irradiated head and neck tumor patients, although the results are inconclusive regarding approach, type of therapy, proper timing, and dose [12, 20, 27–29]. Surgical therapeutic procedures, as is the widespread standard of care in Germany, are poorly represented in the literature [27, 30]. Similarly, a Cochrane systematic review and another review revealed great heterogeneity in terms of study design, methodology, and the effectiveness of prophylactic swallowing exercises and encouraged further methodologically well-designed studies to better classify methods and their outcome measurement [4, 31]. Recent studies from other healthcare systems, such as the English NHS, have already demonstrated the feasibility of pre-therapeutic swallowing intervention in patients with advanced tumor stages (UICC III/IV) [32].

In many cases, however, patients are discharged from oncological care who are exclusively or substantially dependent on non-oral forms of nutrition, burdened with an uncertain prospect of at least partial recovery of natural function. The focus on post-therapeutic rehabilitation and separation from the care at the oncological centers combines restrictions on the individual possible therapy success with the danger of a reduced use of rehabilitative measures, because of a lack of education and motivation of the patients.

According to clinical experience, such preventive rehabilitative approaches are almost completely lacking in routine care in Germany [33]. Although the therapy of head and neck tumors at oncological centers today usually achieves what is necessary and possible, the rehabilitation of functional deficits is shown to be comparatively incomplete. The benefit of pre-therapeutic evaluation and intervention is hinted at in the current AWMF (*Arbeitsgemeinschaft der Wissenschaftlichen Medizinischen Fachgesellschaften e. V.*) organ guidelines, the S3 guidelines on oral cavity carcinoma [9] and laryngeal carcinoma [8], but recommendations regarding approach, type of therapy, timing, and dose remain vague. The preoperative or pre-therapeutic preparation of patients for these expected therapeutic consequences thus remains inadequate.

Thus, there is an urgent need to evaluate the existing evidence for the potential benefit of pre-therapeutic phoniatric intervention in a study setting with a realistic outcome model at a German Head and Neck Cancer Center.

### Improvement of care

The introduction of rehabilitative elements of pre-therapeutic phoniatric intervention, at the earliest possible time before and during acute therapy, has considerable potential to improve care:Improvement of swallowing function represents, in the first place, a significant contribution to quick recovery and a crucial contribution not only to QoL (regaining oral nutrition and social reintegration, especially of socially disadvantaged patients), but also to patient safety (prevention of malnutrition and aspiration pneumonia).Suffering and burden of patients with head and neck tumors and the high prevalence of swallowing disorders demonstrate the great need. Data in the literature indicate a high appropriateness of the planned intervention and suggest a relevant improvement in routine care.Information about dysphagia as a consequence of disease and therapy first contributes significantly to patient education, not only to identify existing disorders, but also to name expected disorders and to offer therapeutic options, to assess their nature, possibilities, and limitations in a very specific way in each individual case. This education thus makes a significant contribution to participation; in combination with an exercise program, it strengthens self-efficacy (empowerment).With greater efficiency and time economy, the application and adaptation of existing OPS codes (8–553) for prehabilitation, which are graded according to the amount of work involved, would also make sense from a cost-economic point of view.The cost-effectiveness of the statutory health insurance (SHI) system enhances in two ways, on the one hand by improving the oncological outcome (reduction of morbidity of aspiration pneumonia) and the functional outcome (regaining oral nutrition and social reintegration), and on the other hand by cost savings (costs for non-oral nutrition, inpatient treatment costs, including intensive care).

### Utilization potential

From the perspective of the SHI system, cost-saving potentials are of considerable interest. If the concept of prehabilitation proposed here proves successful, these will result in a reduction in non-oralization (costs of gastric feeding), complications (aspiration pneumonia), and inpatient stays. In sum, this may lead to an increase in the rate of occupational reintegration, which is of considerable importance, especially in patients of socially weaker status. For both increasingly younger and older patients, a successful concept of prehabilitation suggests an improvement in overall outcome, which should be reflected in the alleviation of individual suffering, reduction in family stress, and relief for society as a whole. After sharpening the focus, the results of the proof-of-concept study should be used to initiate a multicenter confirmation study, e.g., within the framework of the BZKF (Bavarian Center for Cancer Research, Head and Neck Tumor Study Group) or even nationwide programs. In addition, it is conceivable that phoniatric prehabilitation can also be offered across sectors in an outpatient setting, for example involving logopedic and ENT specialist practices, prior to the start of oncological therapy. The results of the study will also be used to further develop guidelines in this field within the national AWMF system.

